## 8.2 Safety and Other Assessments

Other measures for this trial include the Cannabinoid Use Survey. Because this is a study of a behavioral intervention, related adverse events (AEs) and serious adverse events (SAEs) are not expected. While the study team will not solicit AEs or SAEs, given the minimal biological/medical risk of the study, the study will provide all participants with a telephone number to report AEs/SAEs. All reported AEs will be evaluated for severity, action taken, seriousness, outcome, and relationship to the study intervention. The study team will track and record all AEs that are severe, serious, and/or related to the study intervention. AEs and SAEs will be collected for both the parent and infant on this study.

## 8.3 Adverse Events and Serious Adverse Events

### 8.3.1 Definition of Adverse Events (AE)

An AE is defined as any untoward medical occurrence associated with the use of an intervention in humans, whether or not considered intervention related.

### 8.3.2 Definition of Serious Adverse Events (SAE)

We will consider an AE or suspected adverse reaction to be “serious” if, in the view of the PIs, medical monitor, or DSMB, it results in any of the following outcomes:

- Death
- Life-threatening AE
- Inpatient hospitalization or prolongation of existing hospitalization
- Persistent or significant incapacitation or substantial disruption of the ability to conduct normal life functions
- Congenital anomaly/birth defect

Important medical events that may not result in death, be life-threatening, or require hospitalization may be considered serious when, based upon appropriate medical judgment, they may jeopardize the participant and may require medical or surgical intervention to prevent one of the outcomes listed in the SAE definition.

### 8.3.3 Classification of an Adverse Event

#### 8.3.3.1 Severity of Event

The site research team will use the following guidelines to describe severity. The site investigator will determine severity.

- **Mild:** Event requires minimal or no treatment and does not interfere with the participant’s daily activities.
- **Moderate:** Event results in a low level of inconvenience or concern with the therapeutic measure. Moderate events may cause some interference with functioning.
- **Severe:** Event interrupts a participant’s usual daily activity and may require systemic drug therapy or other treatment. Severe events are usually potentially life-threatening or incapacitating. Of note, the term “severe” does not necessarily equate to “serious.”

#### 8.3.3.2 Relationship to Study Intervention

The site research team will grade the degree of certainty about causality by using the following categories:

- **Related:** The AE is known to occur with the study procedures, there is a reasonable possibility that the study procedure caused the AE, or there is a temporal relationship between the study procedures and the event. Reasonable possibility means that there is evidence to suggest a causal relationship between the study procedures and the AE.
- **Not Related:** There is not a reasonable possibility that the study procedures caused the event, there is no temporal relationship between the study procedures and the event onset, or an alternate etiology has been established.

#### 8.3.3.3 Expectedness

The site investigator or qualified clinical designee will be responsible for determining whether a severe AE or SAE is expected or unexpected. A severe AE or SAE will be considered unexpected if the nature, severity, or frequency of the event is not consistent with risk of the underlying chronic medical condition, or is not an event measured in study data collection (hospitalization, ED visit etc.), or is not related to function of the study intervention.

Potential expected event could include the following:

- Common illnesses and infections associated with the following organ classes:  Respiratory, Gastrointestinal, Skin, Eyes, Ears, etc.
- Developmental delay
- Slow/poor weight gain
- Need for emergency room visits secondary to physical injuries (including but not limited to falls, concern for fractures or nursemaid's elbow)
- Various neurological disorders and/or deficiencies

### 8.3.4 Time Period and Frequency for Event Assessment and Follow-Up

For this study, the protocol study team will collect all severe AEs, SAEs, and AEs related to the study procedures. The occurrence of a SAE may come to the attention of study personnel during the hospital stay, by the clinical team with administration of questionnaires, or by the medical monitor upon reviewing data. The site research team will capture all AEs on the appropriate case report form following the instructions and timelines provided in the MOP. Information to be collected includes event description, date/time of onset, date/time of resolution, clinician’s assessment of severity, relationship to study intervention and time of resolution/stabilization of the event. Site research teams must follow all severe and SAEs until there is resolution, the condition stabilizes, the event is otherwise explained or judged by the site PI or a qualified clinician designee to be no longer clinically significant, or the participant is lost to follow-up.

Any medical condition that is present at the time the participant is screened will be considered as baseline and not reported as an AE. However, at the onset of the intervention and anytime during the study, if the study participants condition deteriorates and meets the definition of a severe AE or SAE, it will be recorded as an AE. Changes in the severity of an AE will be documented to allow an assessment of the duration of the event at each level of severity to be performed.

### 8.3.5 Adverse Event Reporting

Site coordinators and/or the study team will record all severe and related AEs in the electronic data capture (EDC) system, include them in the statistical analysis, and follow the reporting procedures outlined in the trial-specific MOP. The MOP section on reporting severe AEs will encompass the requirements of:

1. Reviewing IRB’s policies and procedures
2. Standard Operating Procedures (SOPs) for the Streamlined, Multisite, Accelerated Resources for Trials IRB Reliance platform (SMART IRB)
3. ICH E6(R2), GCP: Integrated Addendum to ICH E6(R1): Guidance for Industry
4. Following local IRB’s policies and procedures, when applicable. If there are discrepancies between the procedures, we will follow the most stringent of the procedures.

If there are discrepancies between the procedures, we will follow the most stringent of the requirements.

The DCOC will report severe and related AEs to the cIRB for its yearly continuing review. The DCOC will report to the Central IRB (cIRB), as specified in the study-specific IRB communication plan, which is based on recommendations from the SMART IRB agreement. Sites will also report severe AEs to the local IRB, per local IRB policies and procedures, and make them available to the sponsor (DCOC) on a continuing basis through the EDC system. The study team/sponsor will report to the DSMB, per the DSMB charter.

The trial-specific MOP will describe the details of the reporting structure and additional details related to timelines for reporting.

### 8.3.6 Serious Adverse Event Reporting

The clinical coordinator will record all SAEs in the EDC and the DCOC will report SAEs. The DCOC will notify monitoring personnel (e.g., medical monitor) and monitoring bodies (e.g., DSMB), per the DSMB charter. The DCOC will make these reports whether or not the trial clinician or medical monitor consider the event trial-intervention related. Reports must include an assessment of whether there is a reasonable possibility that the trial intervention caused the event. Reports to the reviewing IRB will be made yearly for continuing review. The reports to the local IRB will be made per local IRB policies and procedures. Reports to the DCOC will be made immediately, within 48 hours of finding out about the event.

Study personnel will follow all SAEs until satisfactorily resolved or the ISPCTN site investigator deems the event is chronic, or the participant is stable.

### 8.3.7 Reporting Events to Participants

We will notify participants of those trial-related (or potentially trial-related) SAEs that may affect their willingness to continue with the trial or the future health of the mother or the infant. Any of the following can determine if study personnel should contact participants: the IRB, the medical monitor, the DSMB, or the PIs. The person or oversight body that makes the determination will inform the DCOC, which will instruct the ISPCTN site investigators and coordinators to contact the participants enrolled through their site.

ISPCTN site research staff will record any contact with participants, if necessary, in the EDC and/or trial log.

### 8.3.8 Events of Special Interest

We have not identified other reportable events for this trial.

### 8.3.9 Reporting of Pregnancy

We will not report pregnancies for this trial.

## 8.4 Unanticipated Problems

### 8.4.1 Definition of Unanticipated Problems (UP)

The Office for Human Research Protections considers unanticipated problems (UPs) involving risks to participants or others to include, in general, any incident, experience, or outcome that meets all the following criteria:

- Unexpected in terms of nature, severity, or frequency given 1) the research procedures that are described in the protocol-related documents, such as the IRB-approved research protocol and informed consent document; and 2) the characteristics of the participant population being studied; AND
- Related or possibly related to participation in the research (“possibly related” means there is a reasonable possibility that the incident, experience, or outcome may have been caused by the procedures involved in the research); AND
- Suggests that the research placed participants or others at a greater risk of harm (including physical, psychological, economic, or social harm) than study personnel previously knew or recognized.

An UP is not necessarily an AE or an SAE, but study personnel must report these. For example, a breach of confidentiality is an example of an UP that is not an AE or SAE. The UP report will include the following:

- Protocol identification information
- A detailed description of the event, incident, experience, or outcome
- An explanation of the basis for determining that the event, incident, experience, or outcome represents an UP
- A description of any changes to the protocol or other corrective actions that have been taken or are proposed in response to the UP

### 8.4.2 Unanticipated Problem Reporting

Study personnel must report UPs to the reviewing IRB, via the method(s) specified in the MOP, and directly to the DCOC. The DCOC will notify the PIs and the DSMB. Other persons or groups will receive reports as specified in the DSMB charter. Study personnel must report these UPs to the reviewing IRB according to its policies and procedures and report to local institutions according to the rules and regulations of the local institution. An unexpected death or life-threatening event will be reported immediately to the IRB office or IRB chair. All other unexpected events will be reported within 10 days of the event or notification of the event if non-local.

### 8.4.3 Reporting Unanticipated Problems to Participants

For reporting UPs to participants, we will follow the same procedures as described for reporting events to participants.

# 9 Statistical Considerations

## 9.1 Statistical Hypotheses

| **Objectives:** | \| **Primary Objective:** Conduct a rigorous feasibility pilot study of a novel program to improve neurodevelopmental outcomes in infants prenatally exposed to cannabinoids as the basis for a future randomized controlled trial. We will conduct the feasibility trial in three ISPCTN sites to assess the following variables: participant recruitment, participant completion when the infant is 12 months of age, and completion of overall total number of INTACT intervention coaching sessions. This information will inform a future randomized controlled trial, at which time a clinical outcome assessment with the Bayley Scales of Infant and Toddler Development Screening Test, 4^th^ Edition (Bayley-IV) will be completed at 2 years of age. Thus, no clinical outcome assessment will be completed in this feasibility pilot study.  **Objective 1: Participant Recruitment:** To examine if birthing parents can be approached, consented, and determined to be eligible in the study utilizing multi-faceted recruitment approaches, which may include distributing flyers in the obstetrical and family medicine clinics (for individuals with self-report) and utilizing electronic health record (EHR) review to identify and approach pregnant and post-partum individuals with positive toxicology screen(s). Providers may give flyers individually to birthing parents in the obstetrical and family medicine clinics if the individual uses cannabinoids in pregnancy. All birthing parents approached by the study team for study participation will be tracked. **Hypothesis:** The percentage of participants approached, consented, and determined to be eligible for study participation will be greater than 20% of those approached, consistent with other similar feasibility studies.  **Objective 2: Participant Completion:** To evaluate participant completion, as measured by the percent of birthing parent/infant dyads that complete the final coaching session scheduled when the child is 12 months of age (recruitment goal of n=20 dyads) compared to the number of individuals approached, consented, and determined to be eligible. **Hypothesis:** This study will have participant completion of at least 70% (n≥14) at the final visit when the child is 12 months of age.  **Objective 3: Participant Adherence:** To evaluate the number of individual INTACT intervention coaching sessions completed. This will be measured by the total number of sessions completed compared to the total number of possible sessions (n=12 sessions) for the individuals approached, consented, and determined to be eligible for study participation. **Hypothesis**: 80% (n≥16) of the participants will receive a sufficient number of INTACT intervention coaching sessions completed, defined as at least 8 of the 12 sessions.^1^ \| \| --- \| |
| --- | --- | --- |
| **Endpoints:** | \| Primary Endpoints:   1. Whether a potential participant approached for study participation will eventually be consented and determined to be eligible for study participation. 2. Whether a birthing parent/infant dyad will complete the final coaching session when the child is 12 months of age. 3. Whether a birthing parent/infant dyad will complete the sufficient number of INTACT intervention coaching sessions, defined as completion of at least 8 out of 12 coaching sessions. \|  \| \| --- \| --- \| |

## 9.2 Sample Size Determination

In **Objective 1,** we anticipate 20 eligible dyads will be approached, consented, and determined to be eligible for study participation, yielding a targeted rate of recruitment of at least 20% of the approached population. A null hypothesis of a rate of 10% will be rejected with 0.89 power using a one-sided exact test at 0.05 significance level.

The intent of **Objective 2** is to determine if the retention rate is ≥70%. We anticipate at least 14 dyads will complete the final coaching session for a retention rate of 70% or above. With 20 participants, the null hypothesis that the retention rate is 40% can be tested against the alternative that it is 70% at the one-sided 0.05 significance level with a power of 0.88. With 20 participants, the null hypothesis will be rejected if the number of participants who are retained is ≥14.

The intent of **Objective 3** is to determine if the participant adherence rate is ≥80%. We anticipate at least 16 out of 20 birthing parent/infant dyad will complete the required number of INTACT intervention coaching sessions. With 20 participants, the null hypothesis that the adherence rate is 50% can be tested against the alternative that it is 80% at the one-sided 0.05 significance level with a power of 0.90. With 20 participants, the null hypothesis will be rejected if the number of participants who are adherent is ≥16.

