## 9.4 Statistical Analyses

### 9.4.1 General Approach

Following finalization of the protocol, but prior to data lock, the DCOC statistical team will issue a Statistical Analysis Plan (SAP) as a separate document, which will provide detailed analytical plans for the set of analyses outlined below. The statistical team will conduct all statistical analyses following the statistical principles for clinical trials as specified in ICH Statistical Principles for Clinical Trials (ICH Topic E9). The study team will describe and justify any deviations from the planned analyses in the final integrated clinical study report. The study team will present all study data and summary tables for the overall study and by study sites.

**Descriptive Statistics:** At baseline, demographics and cannabinoid usage based on the Cannabinoid Use Survey will be collected. All numerical variables will be summarized using mean ± standard deviation and median (minimum, maximum). All categorical variables will be summarized using frequency (in %).

**Statistical Inference:** Considering the small sample size proposed in the pilot study, exact methods will be used in statistical inference. Hypothesis tests will be one-sided with a significance level of 0.05.

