### 9.4.2 Analysis of the Primary Efficacy Endpoint(s)

**Objective 1: Participant Recruitment.**

The primary endpoint of recruitment will be summarized using frequency (in %). A one-sided exact Clopper-Pearson (or exact) test will be used to test against a null rate of 10%.

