**Objective 2: Participant Completion.**

The endpoint of study completion of required study assessments (or participant completion) will be summarized using frequency (in %). A one-sided exact Clopper-Pearson (or exact) test will be used to test against a null rate of 40%.

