**Objective 3: Participant Adherence.**

The endpoint of completion of a sufficient number of INTACT intervention coaching sessions (or participant adherence) completed will be summarized using frequency (in %). A one-sided exact Clopper-Pearson test will be used to test against a null rate of 50%.

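### Objectives 2 and 3: the rejection cut-offs in 9.2 are not those of the exact 0.05 tests in 9.4, the stated powers fit neither, and rejecting 10%, 40% or 50% does not establish the target rates

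*Protocol*

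**What the plan says.** **Section 9.1** gives the hypotheses. Recruitment "will be greater than 20% of those approached"; completion is at least 70%, given as 14 or more dyads; adherence is 80%, given as 16 or more.

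**Section 9.2** says that the intent of Objective 2 "is to determine if the retention rate is ≥70" percent, and says the same of 80% for Objective 3. With 20 participants it then sets:

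- Objective 2: null 40%, alternative 70%, reject at 14 or more, power 0.88.
- Objective 3: null 50%, alternative 80%, reject at 16 or more, power 0.90.
- Objective 1: null 10%, power 0.89, with a target of at least 20%. It gives neither a number approached nor a cut-off.

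**Section 9.4.1** says that "exact methods will be used in statistical inference" and that "Hypothesis tests will be one-sided with a significance level of 0.05".

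**Section 9.4.2** names the tests but no cut-offs. Objective 1: "test will be used to test against a null rate of 10" percent. Objective 2: "A one-sided exact Clopper-Pearson (or exact) test will be used to test against a null rate of 40" percent. Objective 3: "A one-sided exact Clopper-Pearson test will be used to test against a null rate of 50" percent.

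**The concern.** Three things do not fit together.

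- Sections 9.2 and 9.4 apply different rejection rules to the same null for two of the three primary endpoints, so one result could be reported either way.
- The cut-offs in 9.2 equal the target counts in 9.1 (70% and 80% of 20). They read like point-estimate targets entered as critical values, and the powers beside them look too high for such strict rules.
- The tested rates (10%, 40%, 50%) lie well below the rates the trial says it will determine.

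These endpoints are meant to inform a future randomised trial. With two rules in force, the choice between them could be made after the data are seen.

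**Working it through.** **Inputs.** n = 20, nulls, alternatives, cut-offs and powers from 9.2; one-sided 0.05 and exact methods from 9.4.1; tests from 9.4.2.

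**Step 1. The stated powers.** The one-sample normal approximation is

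power = Φ{ [(p1 − p0)√n − 1.645√(p0(1 − p0))] / √(p1(1 − p1)) }.

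- Objective 2: (0.3 × 4.472 − 1.645 × 0.490) / 0.458 = 1.169, giving 0.879.
- Objective 3: (0.3 × 4.472 − 1.645 × 0.5) / 0.4 = 1.298, giving 0.903.

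These match 0.88 and 0.90, so the stated powers are consistent with a normal approximation, although 9.4.1 requires exact methods.

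**Step 2. Exact alpha and power.** For X ~ Bin(20, p), alpha(r) = P(X ≥ r | p0) and power(r) = P(X ≥ r | p1).

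| Objective | Reject if | Exact alpha | Exact power |
|---|---|---|---|
| 2 (40% v 70%) | ≥12 | 0.0565 | 0.887 |
| 2 | ≥13 | 0.0210 | 0.772 |
| 2 | ≥14 (9.2) | 0.0065 | 0.608 |
| 3 (50% v 80%) | ≥14 | 0.0577 | 0.913 |
| 3 | ≥15 | 0.0207 | 0.804 |
| 3 | ≥16 (9.2) | 0.0059 | 0.630 |

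The exact 0.05 tests reject from 13 and 15. No cut-off that keeps alpha at or below 0.05 reaches 0.88 or 0.90. The next lower cut-offs (12 and 14) give power near the stated values but exceed 0.05.

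**Step 3. How often the two rules disagree.** They differ on a single count.

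- P(X = 13 | 20, 0.7) = 0.164
- P(X = 15 | 20, 0.8) = 0.175

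**Step 4. What a rejection shows.** One-sided 95% Clopper-Pearson lower bounds:

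- 13/20: 44.2%; 14/20: 49.2%
- 15/20: 54.4%; 16/20: 59.9%

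A result that meets the 9.1 target still leaves rates well below 70% or 80% compatible with the data. Testing the targets themselves at 0.05 would need 18/20 against 70% (alpha 0.0355) and 20/20 against 80% (alpha 0.0115; 19/20 gives 0.0692).

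Probability of rejecting when the true rate is 10 points below target:

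- Objective 2, true 60%: 0.25 at ≥14; 0.42 at ≥13.
- Objective 3, true 70%: 0.24 at ≥16; 0.42 at ≥15.

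**Step 5. Objective 1.** With 20 eligible dyads, the largest N for which P(Bin(N, 0.1) ≥ 20) ≤ 0.05 is 135 (p = 0.048), so 20/135 = 14.8% rejects 10%.

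N = 100 is an assumption (20 / 0.20), since the protocol gives no N. There the test rejects from 16 (p = 0.040), with exact power 0.871 and normal-approximation power 0.897, against the stated 0.89. Cut-offs at other values of N:

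| N approached | Reject from | Observed rate |
|---|---|---|
| 50 | 10 | 20.0% |
| 60 | 11 | 18.3% |
| 80 | 14 | 17.5% |
| 90 | 15 | 16.7% |
| 100 | 16 | 16.0% |
| 110 | 17 | 15.5% |
| 120 | 19 | 15.8% |

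Of the values checked, all from 60 up allow rejection below 20%. Separately, exactly 20% meets the target in 9.2 (at least 20%) but fails the hypothesis in 9.1 (greater than 20%).

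**The case against.** The strongest reply is that 9.2 contains the only cut-offs in the protocol, and they coincide with the targets in 9.1. Rejecting at 14 and 16 is a valid, conservative exact test, with alpha far below 0.05. On that reading 13/20 and 15/20 fail both test and target. This stands as far as it goes: a reader might infer that 13/20 and 15/20 simply pass the planned test, or that 13 and 15 are the only correct cut-offs, and the protocol supports neither. They pass only when 9.4 is applied as a plain 0.05 test. The rejection probabilities of 0.42 likewise belong to 13 and 15; at the stated cut-offs they are 0.25 and 0.24.

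Setting the null at an unacceptable rate and the alternative at the target is also a standard single-arm design. Section 8.1 already words 20%, 70% and 80% as aims, and 9.4.2 reports observed frequencies. Nothing says that a significant test will be cited as proof of 70% or 80%, and no go/no-go rule for the future trial is given. That is fair. The fault lies in the wording of intent in 9.2 and in the lack of one governing rule, not in the choice of nulls.

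For Objective 1, a result of 16 to 19 out of 100 rests on an assumed N. It would also need recruitment to end short of 20 assigned dyads, for instance at the cap of 50 consents in 10.1.1. The 20/135 example does not depend on assuming N = 100.

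None of this rescues the stated powers, which fail under either rule.

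**Conclusion.** The point holds in this form. For Objectives 2 and 3, sections 9.2 and 9.4 give rejection rules that differ by one count, so they disagree with probability 0.16 at a true 70% and 0.17 at a true 80%. The stated powers of 0.88 and 0.90 are overstated under both rules: by about 27 points at the 9.2 cut-offs (0.88 − 0.61; 0.90 − 0.63) and by 10 to 11 points at 13 and 15 (0.90 − 0.80; 0.88 − 0.77). For all three objectives, rejecting the null does not determine that the target rate is met.

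The figures for Objectives 2 and 3 assume a denominator of exactly 20, as 9.2 does. Objective 1 has no competing cut-off in 9.2. Its problem is the distance between the 10% null and the 20% target, together with the two wordings of that target.

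**What to change.** State one governing rule per objective, the same in 9.2 and 9.4.2. For Objectives 2 and 3 either option works:

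- **Keep 14 and 16** as the declared cut-offs in both sections, with exact alpha 0.0065 and 0.0059 and power 0.61 and 0.63. Test and target then coincide.
- **Use the exact 0.05 cut-offs 13 and 15**, with alpha 0.021 each and power 0.77 and 0.80, and make the observed 70% and 80% targets a separate feasibility criterion. State in advance how a result that rejects the null but misses the target will be reported.

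In either case:

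- Replace 0.88 and 0.90.
- Word the test conclusions as the rate exceeding 10%, 40% or 50%, and reword the intent in 9.2 to match.
- Report each observed rate against its 20%, 70% or 80% target with a two-sided 90% Clopper-Pearson interval, whose lower limit matches the one-sided 0.05 test.
- For Objective 1, choose between greater than 20% and at least 20%, and state the number approached that the power of 0.89 assumes.

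The cost is a few sentences in 9.1, 9.2 and 9.4.2, with no new data or participants. The downside is a lower stated power and a more modest claim.

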| **Endpoints:** | \| Primary Endpoints:   1. Whether a potential participant approached for study participation will eventually be consented and determined to be eligible for study participation. 2. Whether a birthing parent/infant dyad will complete the final coaching session when the child is 12 months of age. 3. Whether a participant will complete the sufficient number of INTACT intervention coaching sessions, defined as completion of at least 8 out of 12 coaching sessions. \|  \| \| --- \| --- \| |
| **Study Population:** | Sample size n=20 (6-7 participants per site, 3 Institutional Development Award (IDeA) States Pediatric Clinical Trials Network [ISPCTN] sites). |
| **Phase:** | Pilot |
| **Description of Sites/Facilities Enrolling Participants:** | The study team will conduct the INTACT trial at three ISPCTN site-awardee states. The study team will enroll participants into the INTACT trial from one hospital per ISPCTN-awardee state. |
| **Description of Study Intervention:** | The study intervention is described below:   - The birthing parent/infant dyad will complete 12 monthly INTACT intervention coaching sessions, each of which consists of online module completion followed by a personalized coaching session. Individuals will complete the online module each month prior to the coaching session with an interventionist. - Each of the online modules contains information to strengthen effective parenting practices that promote early language, cognitive, and social development. Parenting skills that are introduced in the online module will be reinforced with the monthly coaching session. - During the monthly coaching sessions, the coaches will guide the birthing parent on contingent responding, which includes “reading infant signals, responding with warm and sensitive behaviors, maintaining infants’ focus of attention, watching for opportunities to introduce an object or social game, using rich verbal content in combination with physical demonstrations and incorporating this constellation of behaviors in everyday activities”.^1^ |

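### Stated powers of 0.88 (Objective 2) and 0.90 (Objective 3) are not delivered: under the stated rejection rules exact power is 0.61 and 0.63

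*Protocol*

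**What the plan says.** The Synopsis (1.1) sets the size of the pilot: "Sample size n=20 (6-7 participants per site, 3 Institutional Development Award (IDeA) States Pediatric Clinical Trials Network [ISPCTN] sites". Section 9.2 then gives a full test specification for each of two primary objectives.

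- **Objective 2, completion of the month-12 session.** The null rate is 40% in 20 dyads. For the rate hoped for, the section reads: "it is 70% at the one-sided 0.05 significance level with a power of 0.88". The decision rule comes next: "the null hypothesis will be rejected if the number of participants who are retained is ≥14".
- **Objective 3, at least 8 of 12 sessions.** The null rate is 50%, again in 20 dyads. For the rate hoped for, the section reads: "it is 80% at the one-sided 0.05 significance level with a power of 0.90". The decision rule is: "the null hypothesis will be rejected if the number of participants who are adherent is ≥16".

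On method, section 9.4.1 cites the small sample and says that "exact methods will be used in statistical inference", one-sided at 0.05. Section 9.4.2 names one-sided exact (Clopper-Pearson) tests against 40% and 50%. Section 9.3 makes consented dyads with confirmed eligibility the analysis population for both objectives, so no allowance for dropout enters the power figure.

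**The concern.** Sample size, null rate, alternative rate and rejection count together determine the power of a single-arm binomial test. Section 9.2 gives all four for each objective, and the power printed beside them does not follow.

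Completion and adherence are two of the three primary endpoints. Section 2.1 treats them as key inputs to the future randomised trial, and section 4.2 has the larger trial follow once feasibility is established. A reader of 9.2 would put the risk of a false negative at 12% for Objective 2 and 10% for Objective 3. If the real risk is several times that, a pilot that fails to reject could be read as stronger evidence of infeasibility than it is.

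**Working it through.** **Inputs** (protocol 9.2): n = 20; one-sided alpha 0.05. Objective 2: p0 = 0.40, p1 = 0.70, reject if X ≥ 14. Objective 3: p0 = 0.50, p1 = 0.80, reject if X ≥ 16.

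**Step 1. Reproduce the stated powers.** The one-sample normal approximation, with null variance in the critical value and no continuity correction, is

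power = Φ( [p1 − p0 − 1.645·√(p0(1−p0)/n)] / √(p1(1−p1)/n) )

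- Objective 2: (0.30 − 1.645 × 0.1095) / 0.1025 = 1.17, so power = 0.879, stated as 0.88.
- Objective 3: (0.30 − 1.645 × 0.1118) / 0.0894 = 1.30, so power = 0.903, stated as 0.90.

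Both printed figures are recovered. With a continuity correction the same formula gives 0.823 and 0.846.

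The critical values behind the uncorrected formula are 20 × (0.40 + 1.645 × 0.1095) = 11.6 and 20 × (0.50 + 1.645 × 0.1118) = 13.7. In whole dyads that means rejecting at 12 and 14, two below the counts printed in 9.2.

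**Step 2. Exact operating characteristics.** With X ~ Binomial(20, p), type I error is P(X ≥ r | p0) and power is P(X ≥ r | p1).

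| Objective | Reject at | Type I error | Power | Status |
| --- | --- | --- | --- | --- |
| 2 | ≥12 | 0.0565 | 0.887 | exceeds 0.05 |
| 2 | ≥13 | 0.0210 | 0.772 | exact 0.05-level test |
| 2 | ≥14 | 0.0065 | 0.608 | rule in 9.2 |
| 3 | ≥14 | 0.0577 | 0.913 | exceeds 0.05 |
| 3 | ≥15 | 0.0207 | 0.804 | exact 0.05-level test |
| 3 | ≥16 | 0.0059 | 0.630 | rule in 9.2 |

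At n = 20 the only cut-offs that reach the printed powers break the stated alpha.

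**Step 3. Split the shortfall.** Two causes add up.

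- Normal approximation instead of the exact test: 0.88 to 0.77, and 0.90 to 0.80.
- A rejection count one higher than the exact 0.05 test needs: 0.77 to 0.61, and 0.80 to 0.63.

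The second cause is also a conflict within the protocol. With 13 completers (p = 0.021) or 15 adherent dyads (p = 0.021), the test in 9.4.2 rejects and the rule in 9.2 does not. Under the alternatives, those single outcomes have probability 0.772 − 0.608 = 0.164 and 0.804 − 0.630 = 0.174.

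**Step 4. False-negative risk when the true rates are 70% and 80%.**

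| Objective | As stated | Exact 0.05-level test | Rule in 9.2 |
| --- | --- | --- | --- |
| 2 | 0.12 | 0.228 (1.9 times) | 0.392 (3.3 times) |
| 3 | 0.10 | 0.196 (2.0 times) | 0.370 (3.7 times) |

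**The case against.** The strongest reply is that 14 and 16 are feasibility targets (70% and 80% of 20, as in sections 1.1, 3 and 9.1) that were carried into 9.2, and that the analysis actually prescribed is the exact test in 9.4.2. On that reading the powers are 0.77 and 0.80, the false-negative risk is 20 to 23%, and 0.61 and 0.63 are the worst case. This stands as a description of the range. It does not rescue the printed figures, because 9.2 plainly presents 14 and 16 as rejection rules and neither reading reaches 0.88 or 0.90.

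It can also be said that the figures are not arbitrary, since a standard approximation reproduces them, and that 9.2 mentions an exact test only under Objective 1. That is true, but 9.4.1 and 9.4.2 require exact tests for Objectives 2 and 3 as well, and the approximation implies cut-offs that 9.2 does not use.

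Finally, this is a pilot with no clinical outcome, and no passage makes the future trial depend formally on rejecting these nulls; section 2.1 calls the data formative. That limits how firmly the consequence can be put. The risk is one of misreading a negative result, not of a written stopping rule misfiring. It does not make a wrong power statement for two primary hypotheses correct.

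One caution about the remedy stands. Rejecting at 13 or 15 corresponds to 65% or 75%, so the null could be rejected while the 70% or 80% target is missed. The text would have to keep the two criteria apart.

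**Conclusion.** The concern holds. Under the rejection rules in section 9.2, exact power is 0.61 for Objective 2 and 0.63 for Objective 3, about 27 percentage points below the stated 0.88 and 0.90. Under the best exact one-sided 0.05 test at n = 20 it is 0.77 and 0.80, about 10 points below. No reading of the protocol delivers the printed figures.

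The calculation uses only the protocol's own inputs. It assumes 20 dyads in the analysis, independent outcomes, and true rates equal to the stated alternatives. The Objective 1 power was not part of this check.

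**What to change.** Keep n = 20 and restate section 9.2 in one of two ways, with 9.4.2 and the SAP to match.

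1. **Keep 14 and 16 as the rejection counts.** State power 0.61 with type I error 0.006 for Objective 2, and power 0.63 with type I error 0.006 for Objective 3. Say in 9.4.2 that these counts, not p ≤ 0.05, decide rejection. The hypotheses stay as they are.
2. **Use the exact 0.05-level counts.** Reject at 13 or more (type I error 0.021, power 0.77) and at 15 or more (type I error 0.021, power 0.80). Keep 14 and 16 as separate descriptive feasibility targets, and say how a result of exactly 13 or 15 will be reported.

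Either way, drop 0.88 and 0.90 and say that power was computed by the exact binomial. The cost is a protocol text amendment before results are read, with less favourable powers and no extra participants. The second option also moves the decision boundary for two primary endpoints, so it should be described as a change of rule.

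If powers near the printed ones are wanted, the sample must grow. With 23 dyads, exact rejection at 14 gives 0.880 for Objective 2 and at 16 gives 0.929 for Objective 3. That would also mean changing the limit of 20 assigned dyads in section 10.1.1.
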